#### Data analysis

A description of the sociodemographic and clinical characteristics of the patients involved in this trial will be performed for the complete sample and for each group using a mean with standard deviation or median with interquartile range for the quantitative variables, and using frequencies and percentages for the categorical variables. These characteristics will be compared between the control and experimental groups using parametric tests such as the Student *t* test and Chi-squared test, or nonparametric tests such as the Mann–Witney or Fisher tests. If any of the variables differs significantly between groups, this will be taken into account when comparing the outcomes. The incidence of haemorrhage (pre-, intra- and postoperative) and other categorical secondary variables, such as complications 3 months after surgery, both for the total sample and for each group, will be estimated by means of sample proportion with a 95% confidence interval and from baseline to 3 months after surgery will be compared between groups using parametric or nonparametric tests, such as the Student *t* test and Mann–Whitney test, depending on normality. If any sociodemographic or clinical characteristic differs between groups, lineal and logistic regression models will be used to compare the outcomes between groups, including them as covariates, which will provide adjusted odds ratios for the intervention, together with 95% confidence intervals. Sensitivity analyses will also be performed excluding patients with proliferative vitreoretinopathy or proliferative diabetic retinopathy, patients for whom scleral buckling procedures have been placed, and patients under treatment with acetylsalicylic acid to account for the possible bias induced after having included them. Additionally, a multivariate analysis including age and treatment with acetylsalicylic acid will also be performed to account for possible differences in the distribution of these variables among groups. SPSS software version 21.0 will be used to perform the analysis.

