### Statistics

#### Sample size

Considering that there is no difference in the probability of not having complications between the standard therapy (anticoagulant interruption) and the experimental therapy (no interruption of anticoagulant), and assuming a 95% confidence level and a 96% probability of not having complications, 48 patients are required in each arm (*n* = 48 × 2) in order to have an 80% probability that the upper limit of the confidence interval excludes a difference of over 10% in favour of the standard group. Calculations are performed by Sealed Envelope Ltd.

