The main strength of this trial and the most relevant difference compared to previous studies on the topic is its prospective and randomised design. The most important limitations are the small number of patients to be recruited and the low expected incidence of complications, two circumstances that could make it difficult to achieve results of statistical significance.

In conclusion, with this trial we will attempt to provide novel information assessing the possibility of anticoagulant therapy continuation during PPV. The benefits expected from the change in the current surgical management paradigm of anticoagulated patients would be a decreased risk in the incidence of perioperative thromboembolic events and the possibility of performing surgery without delay and without the need for patients to change their usual anticoagulation protocol to the more complex and less secure substitutive therapy.

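### Baseline significance tests decide whether and how outcomes are adjusted, and the resulting odds ratio cannot be read against the 10-point margin or supported by about 4 expected events

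*Protocol article*

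**What the plan says.** The Data analysis section of the protocol article compares sociodemographic and clinical characteristics between the two arms with significance tests. It then states the consequence twice. First: "If any of the variables differs significantly between groups, this will be taken into account when comparing the outcomes". Later: "If any sociodemographic or clinical characteristic differs between groups, lineal and logistic regression models will be used to compare the outcomes between groups". The variables that differ enter as covariates, and the output is an adjusted odds ratio with a 95% confidence interval. The number of characteristics to be tested is not given.

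A separate sentence adds that "a multivariate analysis including age and treatment with acetylsalicylic acid will also be performed". This model is always run and does not depend on the tests. Proportions with 95% confidence intervals are also reported for each group in every case. Anticoagulant type, the stratification factor under Study randomisation, is not named as a covariate.

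The Sample size section works on another scale. It plans 48 patients per arm, "assuming a 95% confidence level and a 96% probability of not having complications", for an "80% probability that the upper limit of the confidence interval excludes a difference of over 10% in favour of the standard group". The Discussion lists "the low expected incidence of complications" among the trial's main limitations.

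**The concern.** Three things go wrong together.

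- **Chance selects the model.** Allocation is computer-generated and made without investigator influence, so a significant baseline difference is a chance event. It does not show that the variable is prognostic, and a strongly prognostic variable can miss significance. The rule lets the observed data choose both the covariates and the form of the analysis.
- **The effect measure changes.** If the rule fires, the binary comparison becomes an odds ratio. The only criterion in the article is a 10-point risk difference, and an odds ratio has no fixed equivalent to that. The article does not say which result prevails if the two disagree.
- **The data are too sparse for the model.** With about 4 events, ordinary logistic regression has little to work with, and it fails for the treatment term whenever an arm has no events.

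At stake is whether two teams following the text on the same data would reach the same conclusion on non-inferiority.

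**Working it through.** **Inputs.** From Sample size: 48 per arm, 4% with a complication in both arms (100% − 96%), margin 10 points, 80% power. From the Discussion, as a range of published rates: 6.6%, 7% and 11.1%. The number of baseline tests, k, is not stated and is an assumption here.

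**1. The plan's own figure.** n per arm = (z₁₋α + z₀.₈₀)² × 2 × 0.96 × 0.04 / 0.10².
- One-sided α = 0.05: (1.645 + 0.842)² × 0.0768 / 0.01 = 47.5, so 48. The stated size is reproduced (power 80.4% at 48).
- One-sided α = 0.025: (1.960 + 0.842)² × 0.0768 / 0.01 = 60.3, so 61.

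The stated size was therefore computed on the risk-difference scale.

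**2. How often the rule fires by chance alone.** For k independent tests at 5%, P = 1 − 0.95^k.

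| k (assumed) | P(at least one p < 0.05) |
|---|---|
| 5 | 23% |
| 10 | 40% |
| 15 | 54% |
| 20 | 64% |

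**3. What the margin means as an odds ratio.**
- From 4%: (0.14/0.86) / (0.04/0.96) = 3.9.
- From 7%: (0.17/0.83) / (0.07/0.93) = 2.7.

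The same margin is a different odds ratio at each control risk, so an adjusted odds ratio cannot be judged against it without a further assumption.

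**4. Events per parameter.** Expected events = 96 × 0.04 = 3.84. A triggered model with one covariate has three parameters (intercept, treatment, covariate): 3.84 / 3 ≈ 1.3.

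**5. Empty arm.** P(at least one arm has no event) = 1 − (1 − (1 − p)^48)². At 4%: 0.96^48 = 0.141, and 1 − 0.859² = 0.262.

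| Rate in both arms | Expected events | P(at least one empty arm) |
|---|---|---|
| 4% | 3.84 | 26% |
| 6.6% | 6.34 | 7.4% |
| 7% | 6.72 | 6.0% |
| 11.1% | 10.66 | 0.7% |

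In those trials the maximum-likelihood odds ratio for treatment is zero, infinite or undefined.

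**6. Separation on any term.** A simulation of 3,000 trials per scenario added one binary covariate with an assumed 20% prevalence to treatment. Some coefficient diverged in 54% of trials at a 4% rate, 28% at 7% and 11% at 11.1%. Divergence on the covariate alone does not always make the treatment odds ratio infinite, so these are not failure rates for the treatment effect.

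**The case against.** Several stronger readings are tempting, and the article does not support them.

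- **That the adjusted odds ratio is the main estimate and decides the trial.** No estimate is labelled primary, and the group proportions with intervals are always reported. What stands is that the models are to be used for the outcome comparison once the rule fires, and no order of precedence is given. The sentence on the haemorrhage comparison also runs into what reads as the visual acuity analysis, so the intended primary comparison cannot be recovered from it.
- **That one model holds treatment, age, acetylsalicylic acid and every significant variable, with fewer than one event per parameter.** The text describes two analyses. The age and acetylsalicylic acid model is additional and already pre-specified.
- **That the estimate often cannot be computed because of the adjustment rule.** An empty arm defeats any maximum-likelihood odds ratio, adjusted or not. It reaches the triggered analysis only if the rule fires: 0.40 × 0.26 = 10% at k = 10, and 0.64 × 0.26 = 17% at k = 20, before any separation on covariates. At the higher published rates it is much less likely.
- **That the estimate is biased away from the null, or that its interval covers too rarely.** The planning assumption is that "there is no difference in the probability of not having complications between the standard therapy (anticoagulant interruption) and the experimental therapy". With equal arms the log odds ratio is symmetric about zero. The unadjusted Wald interval, where it exists, covers 99.9% of the time at 4%, 99.3% at 7% and 97.2% at 11.1%. The problem there is imprecision, not under-coverage.

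It is also fair to say that a sparse-data method may be set out in an analysis plan that is not shown. Its absence from the article is no fault. The trigger and the odds-ratio output are different: the article fixes both.

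**Conclusion.** The point holds in a limited form. The article prescribes data-driven covariate selection from baseline tests, and for the primary endpoint it turns the comparison into an odds ratio that does not answer the question the trial was sized for. Neither of these depends on the event rate.

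The sparse-data problem adds to them and does depend on the rate. It is serious at the planned 4% (3.84 events, 26% chance of an empty arm) and much smaller at 11.1% (0.7%). The firing probabilities of 23% to 64% rest on an assumed 5 to 20 independent tests; correlated characteristics would change them.

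Visual acuity is analysed by linear regression, so event scarcity does not touch it. It is affected only by the trigger. The change should be made, but the trial remains analysable without it, because the unadjusted proportions are always available.

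**What to change.** In the Data analysis section:

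1. Delete both sentences that make adjustment conditional on a baseline difference, and do not use baseline tests to choose covariates. Describe baseline characteristics by arm only.
2. Name one primary estimate: the difference between arms in the proportion with a haemorrhagic complication, with a score confidence interval, compared with the 10-point margin. This stays computable when an arm has no events. State the level and sidedness of the interval. The article says only "assuming a 95% confidence level", and 48 per arm is reproduced only at one-sided 5%.
3. Keep one supportive model with a fixed list: age and acetylsalicylic acid, which the article already names, and anticoagulant type as the stratification factor. Fit it by a sparse-data method. Penalised (Firth) and exact logistic regression are both acceptable.
4. For visual acuity, drop the trigger in the same way and fix the covariates in advance.

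**Cost.** The wording of the Data analysis section must be revised, and software beyond SPSS 21.0 may be needed; R is already used for the randomisation. The trial gives up post hoc adjustment for chance imbalances in variables outside the list. The sample size formula is not based on a score interval, so power should be rechecked for the interval chosen.

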### Hypothesis

We hypothesise that anticoagulant therapy maintenance before PPV is not associated with a significant increase in perioperative complications compared to those cases in which this therapy is interrupted before surgery, and that the postoperative visual results are not inferior in those cases in which anticoagulant therapy is maintained compared to those cases in which such therapy is interrupted before surgery.

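### The 10-point non-inferiority margin that sets the sample size is not carried into the planned analysis or the stated hypothesis

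*Protocol article*

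**What the plan says.** All references are to the protocol article.

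- **Sample size** assumes that "there is no difference in the probability of not having complications" between the two strategies. It then sets the inputs, "assuming a 95% confidence level and a 96% probability of not having complications", and concludes that "48 patients are required in each arm" to give "an 80% probability that the upper limit of the confidence interval excludes a difference of over 10% in favour of the standard group". This fixes a scale (difference in proportions), a margin (10 points), a direction and a decision rule.
- **Data analysis** plans haemorrhage incidence as a proportion with a 95% interval, overall and by group. It also plans between-group parametric or nonparametric tests. If baseline characteristics differ, it adds linear and logistic models "which will provide adjusted odds ratios for the intervention, together with 95% confidence intervals". Sensitivity analyses and a multivariate analysis follow. The margin does not appear, and neither does an interval for the between-group difference.
- **Hypothesis** states for complications that maintaining therapy "is not associated with a significant increase in perioperative complications". The same sentence uses non-inferiority language for the visual results only, and gives no margin for either outcome.

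**The concern.** The trial is sized to answer one question, and its analysis and hypothesis are written for another. The sample size asks whether an excess of 10 points or more can be ruled out. The hypothesis, as worded, could be met simply by not finding a significant increase.

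With 4% in both arms, about 96 × 0.04 = 3.8 events are expected in the whole trial. Failing to find a difference is then the likely outcome whether or not continuation is harmful. An odds-ratio interval does not close the gap, because a fixed 10-point margin corresponds to a different odds ratio at each control rate. The endpoint includes choroidal and retrobulbar haemorrhage, and the article's stated aim is to support a change in practice, so the rule for concluding safety has to be unambiguous.

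**Working it through.** **1. Reproducing the plan's figure.** Inputs from the Sample size section: 96% complication-free in both arms, margin 0.10, power 80%, 95% confidence (sidedness not stated).

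n per arm = (z_α + z_β)² × 2p(1−p) / margin², with 2 × 0.96 × 0.04 = 0.0768.

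- One-sided 5%: (1.645 + 0.842)² × 0.0768 / 0.01 = 47.5, so **48 per arm**. This matches.
- One-sided 2.5%: (1.960 + 0.842)² × 0.0768 / 0.01 = 60.3, so 61 per arm. This does not match.

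For contrast, a two-sided 5% difference test of 4% against 14% with 80% power needs (1.960√(2 × 0.09 × 0.91) + 0.842√(0.04 × 0.96 + 0.14 × 0.86))² / 0.10², or 128 per arm. So 48 is a non-inferiority size at one-sided 5%.

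**2. Behaviour when harm sits exactly at the margin.** Assumed true rates: 4% (interruption) and 14% (continuation), so 48 × (0.04 + 0.14) = 8.6 expected events. Results are by exact enumeration over two binomial arms of 48.

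| Rule | Probability of a reassuring result |
|---|---|
| Fisher's exact test, two-sided 5%, not significant | 76% |
| Uncorrected chi-squared, two-sided 5%, not significant | 55% |
| Newcombe upper limit below 10 points, one-sided 95% | 4.7% |
| Miettinen-Nurminen upper limit below 10 points, one-sided 95% | 4.1% |

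The article does not legibly assign Fisher or chi-squared to this endpoint, so the first two rows are conditional on that choice.

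**3. A worked outcome.** Suppose 7/48 events with continuation and 2/48 with interruption, a difference of 14.58 − 4.17 = 10.4 points. Fisher p = 0.16 and chi-squared p = 0.08, so neither is significant. The Newcombe upper limit uses the Wilson upper limit for 7/48 (27.17%) and the Wilson lower limit for 2/48 (1.15%):

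10.42 + √[(27.17 − 14.58)² + (4.17 − 1.15)²] = 10.42 + 12.94 = 23.4 points (two-sided 95%).

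The one-sided 95% limit is 21.0 points. Non-inferiority at 10 points is clearly not shown on either.

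**4. The odds ratio and the margin.** At a 4% control rate, 10 points equals an odds ratio of (0.14/0.86) / (0.04/0.96) = 3.9. At assumed control rates of 2% and 11% it is (0.12/0.88) / (0.02/0.98) = 6.7 and (0.21/0.79) / (0.11/0.89) = 2.2. The adjusted odds ratio therefore has no fixed threshold that stands for the margin.

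**5. Power of the margin rule at 48 per arm**, 4% in both arms, one-sided 5%. The normal approximation gives 80.4%. Exact enumeration gives 72% with Newcombe and 64% with Miettinen-Nurminen. With a two-sided 95% Newcombe interval it falls to 49%.

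**The case against.** The strongest reply is that the decision rule is already in the document. The Sample size section gives scale, margin, direction and criterion. This is a condensed article, the full protocol is available on request, and the interval method is commonly left to a statistical analysis plan. That stands for the choice of interval. It does not cover the mismatch, because the article contains its own analysis section and hypothesis, and neither follows the rule that justified the sample size.

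Several stronger readings are tempting and are not supported:

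- *That the plan runs only difference tests on the primary endpoint.* The sentence on haemorrhage incidence in Data analysis is broken and words appear to be missing. The t test and Mann-Whitney test that survive fit the visual acuity change. Chi-squared and Fisher are named only for baseline comparisons. Per-group intervals are also planned. The finding rests on the absent margin, not on any named test.
- *That the odds ratio is the primary analysis.* It arises only if baseline characteristics differ and is nowhere called primary. As a supportive estimate it is not an error.
- *That the Discussion shows success will be judged by significance.* The remark about "two circumstances that could make it difficult to achieve results of statistical significance" is a limitation, not an analysis rule. Authors who worry about missing significance are not obviously treating non-significance as success.
- *That a null test would be reported as proof of safety.* This is an inference. The hypothesis wording allows it but does not say it, and its word for significant is not tied to a statistical test.

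**Conclusion.** The point holds as an inconsistency within the article: the sample size depends on a 10-point non-inferiority criterion that the analysis section never applies and the complications hypothesis does not state. Left as it is, the document supports two different ways of judging the primary outcome, and they can give opposite answers on the same data, as the 7/48 against 2/48 case shows.

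The size is large if a difference test decided the matter: 55% to 76% of trials would look reassuring at an excess equal to the margin, against about 5% under the margin rule. Those figures assume true rates of 4% and 14%, 48 evaluable patients per arm, and Fisher or uncorrected chi-squared as the test, which the article does not confirm. The mismatch itself needs none of these assumptions.

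**What to change.** - **Data analysis:** name as the primary analysis the risk difference (continuation minus interruption) in the composite endpoint, with a score-type interval such as Newcombe or Miettinen-Nurminen. Conclude non-inferiority only if the upper limit is below 10 percentage points. State the level: one-sided 5%, equivalent to a two-sided 90% interval, is the one that reproduces 48 per arm.
- **Hypothesis:** restate the complications part as an increase of less than 10 percentage points.
- **Status of the rest:** make difference tests and odds ratios supportive, and repair the broken sentence on haemorrhage incidence.
- **Sample size:** restate the power for the interval chosen.

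The cost is mainly wording, with no new data to collect. There is one real downside to disclose: at 48 per arm and 4% in both arms, exact one-sided power is about 72% (Newcombe) or 64% (Miettinen-Nurminen), not 80%. If a two-sided 95% interval were preferred instead, the normal-approximation requirement rises to 61 per arm.

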#### Trial governance

The Steering Committee will consist of the Principal Investigator and his research collaborators, which includes clinicians with expertise in ophthalmology. They will be responsible for the recruitment, data collection and completion of case report forms. They will also perform assessments to guarantee adherence to the study protocol. Trial management and data verification will be carried out from the centre’s CTP of Navarrabiomed and data analysis will be conducted by the Unit of Methodology of Navarrabiomed.

#### Regulatory issues

This clinical trial was approved by the local ethics committee (Comité Ético de Investigación con medicamentos de Navarra, Health Department of Navarre Government) and was authorised by the Spanish Agency of Medicines and Medical Devices. This study will be performed in accordance with the standard of Good Clinical Practice and with the current European and Spanish laws that are applicable. The study will be performed in accordance with ethical principles that have their origin in the Declaration of Helsinki and are consistent with International Council for Harmonisation of Technical Requirements for Registration of Pharmaceuticals for Human Use/Good Clinical Practice, and applicable regulatory requirements (Additional file 1).

## Discussion

Vitreoretinal surgery in anticoagulated patients is a complex situation in which retinal surgeons have to choose between being faced with the systemic thromboembolic risks that the interruption of anticoagulation involves, or the intra- and postoperative haemorrhagic risks associated with maintenance of this therapy.

The interruption of anticoagulant therapy before surgery is not innocuous. The risk of thromboembolic events is increased after this treatment is interrupted and during the interval after its re-instauration, when the International Normalised Ratio is below therapeutic levels. The risk associated with the interruption of anticoagulant therapy oscillates between 0.02% in low-risk patients with atrial fibrillation and 0.42% in high-risk patients with artificial heart valves [12]. Cases of serious complications, and even death, have been described in patients who had interrupted anticoagulant treatment before surgery [13–15]. Some investigators have also suggested that anticoagulant therapy interruption could produce a rebound hypercoagulability state due to the alteration of the balance between vitamin K-dependent factors and proteins C and S [16–19]. Moreover, it is a situation that makes it necessary to postpone surgery for a number of days, and this can compromise visual recovery in some surgical indications such as retinal detachment.

There are only a few studies that have evaluated the possibility of anticoagulant therapy continuation before PPV, and most of the authors agree that this circumstance does not involve a particular risk for patients [5–10]. In this respect, Brown and Mahmoud did not find either intraoperative or postoperative complications attributable to the anticoagulation in 27 eyes undergoing diabetic PPV [5]. Chandra et al. did not find an increase in perioperative or postoperative complications of PPV, in particular haemorrhage, in 60 patients taking warfarin [6]. Fu et al. had good visual results in 25 patients undergoing PPV while on warfarin therapy, with only one highly myopic patient suffering a submacular haemorrhage, which resolved spontaneously with a good final visual acuity [7]. Mason et al. describe one transient vitreous haemorrhage (1.6%) among 64 PPVs performed on patients anticoagulated with warfarin, without significant differences from a control group of 110 individuals [8].

Even though some authors have found an increased risk of haemorrhagic complications in anticoagulated patients undergoing PPV, the incidence has been low, without statistical significance, and without serious consequences for visual acuity [9–11, 20, 21]. Dayani and Grand analysed 54 patients who underwent PPV while taking warfarin and found four patients who suffered postoperative vitreous haemorrhage, all of which resolved spontaneously requiring no further surgery [9]. Grand and Walia studied 36 eyes of 33 patients who underwent PPV while being treated with novel anticoagulant therapy and reported that four eyes (11.1%) experienced postoperative vitreous haemorrhage after which two eyes (5.5%) required repeat surgical intervention and two eyes (5.5%) cleared spontaneously [10]. Meillon et al. [11] and Oh et al. [20] report 6.6% and 7% of haemorrhagic complications, respectively, after PPV in patients undergoing anticoagulation therapy, in both studies without visual consequences in the long term. Narendran and Williamson report one case of postoperative choroidal haemorrhage, but only 7 of the 541 patients in their study were taking warfarin during PPV [21].

In contrast to other eye surgeries, vitreoretinal surgery has been considered to pose a high haemorrhagic risk [22]. This means that any perioperative bleeding could have devastating consequences. However, according to the current scientific evidence, this statement cannot be considered to be strictly true. The minor haemorrhagic complications (anterior chamber haemorrhage, vitreous haemorrhage and intraretinal haemorrhage) that can be expected after PPV have a minimal clinical relevance and spontaneous resolution without long-term consequences is usually the norm, with the systemic risk from anticoagulant therapy interruption being much greater. The major haemorrhagic complications are very rare. Most choroidal haemorrhages resolve spontaneously, although some cases with massive haemorrhage and retinal apposition may be difficult to manage. With regard to retrobulbar haemorrhages, they also resolve spontaneously, although their appearance may cause the surgical intervention to be delayed. This circumstance has led to many authors proposing a change in this paradigm and considering PPV as having moderate or even low haemorrhagic risk and considering continuing anticoagulant therapy before surgery [23–25], an assertion that the present trial will attempt to assess.

The main strength of this trial and the most relevant difference compared to previous studies on the topic is its prospective and randomised design. The most important limitations are the small number of patients to be recruited and the low expected incidence of complications, two circumstances that could make it difficult to achieve results of statistical significance.

In conclusion, with this trial we will attempt to provide novel information assessing the possibility of anticoagulant therapy continuation during PPV. The benefits expected from the change in the current surgical management paradigm of anticoagulated patients would be a decreased risk in the incidence of perioperative thromboembolic events and the possibility of performing surgery without delay and without the need for patients to change their usual anticoagulation protocol to the more complex and less secure substitutive therapy.

